## Abstract

**Background:**

Young adults experiencing homelessness (YAEH) have high rates of mental health challenges, yet low rates of mental health service utilization. The transition from homelessness to housing is a key time for intervention to connect YAEH with mental health treatment and provide support to improve both mental health and housing stability. *Charge Up!* is a 6-month, phased support intervention that utilizes a team-based approach to connect young adults to community and mental health support. It is an adaptation of Critical Time Intervention that integrates components of Cornerstone, a mental health support intervention designed for young adults.

**Methods:**

This pilot study uses a phased open trial that begins with a feasibility trial to refine the adapted *Charge Up!* intervention (*n* = 8), then further tests feasibility, acceptability, and preliminary signal of impact in a small, randomized pilot trial (*n* = 52). Participants are young adults moving into a transitional housing to rapid rehousing program (TH/RRH) in Houston, Texas. Quantitative interviews are conducted at baseline, 3 months, 6 months, and 12 months. Qualitative interviews are also conducted at 6 months. Exploratory analyses will examine the feasibility of implementing *Charge Up!*, the performance of measures, and whether *Charge Up!* is changing the hypothesized targets. Qualitative analysis from interviews will examine demand for the intervention, acceptability of the intervention, and integration of the intervention within the housing system context.

**Discussion:**

The aim of this study is to pilot test *Charge Up!*, an adapted version of Critical Time Intervention designed to provide targeted support for mental health at the point of transition from homelessness to housing. The *Charge Up!* intervention was co-developed with young adults and providers, and this phased open trial will help to refine and provide preliminary evidence of the feasibility and acceptability of the intervention. The program is provided in conjunction with a widely used housing model, RRH, and has the potential for scalability as an adjunctive intervention to support youth transitioning into RRH across the United States.

**Trial registration:**

This study was registered on ClinicalTrials.gov on October 20, 2023 (Identifier: NCT06102850), as Protocol ID R34MH129542-01A1, University of Houston, Title: Adaptation of Critical Time Intervention for Young Adults with MH Challenges (CTI-YAMH).

## Introduction

Young adult homelessness is an urgent public health issue with over 3 million young adults experiencing housing instability each year [1]. Over half of young adults experiencing homelessness (YAEH) are impacted by a mental disorder [2], highlighting the urgency of developing interventions to support mental health during the stressful transition from homelessness to housing. Supported housing programs that are funded through the Department of Housing and Urban Development (HUD), such as rapid rehousing (RRH), come with case management support but lack clear guidelines or evidence-based interventions for providing mental health supports in conjunction with housing programming, particularly for young adults. This is becoming increasingly urgent as levels of depression and anxiety have risen in young adults over the last decade [3], particularly in the wake of the COVID-19 pandemic [4].

Prevalence of mental illness is high and growing among young adults. 3.3 million young adults experienced a serious mental illness in 2020, more than double the number reported in 2008 [3]. Young adults that experience housing instability are particularly impacted by mental health problems. Studies examining the prevalence of mental health symptoms have generally found that between 49 and 98% of YAEH meet criteria for a mental disorder [2, 5–7], with 36–67% meeting criteria for two or more diagnoses [2, 7], particularly co-occurring substance use disorders and internalizing disorders such as post-traumatic stress disorder (PTSD) and major depression [7]. About 20–30% of YAEH across studies met criteria for a mood disorder (depression or bipolar) and 5% to 48% met criteria for PTSD [2, 6–8]. This has dire consequences, with YAEH having mortality rates ten times higher than their peers in the general population, primarily due to suicide and drug overdose [9].

YAEH disproportionately come from marginalized groups, highlighting the need to tailor interventions specifically for their needs. In their national household survey of homelessness, Morton et. al. (2018) found that 3.5 million young adults experienced a form of homelessness in the past 12 months and that Black, Hispanic, and Lesbian, Gay, Bisexual, Transgender, and Queer (LGBTQ +) youth were disproportionately affected [1]. These intersecting identities have impacts on mental health and the culturally relevant services needed for treatment [10, 11]. Recent work examining over 1000 YAEH across 7 cities found that experiences of discrimination were widely reported among YAEH and associated with greater psychological distress [12]. Yet, marginalized youth of color, particularly young men, are least likely to seek and receive mental health services [13].

Mental health and housing are closely related. Mental health is fundamentally tied to housing in a bi-directional relationship [14, 15]. Mental health symptoms heighten risk for homelessness in young adults and the experience of being homeless can exacerbate mental health symptoms or trigger onset [14]. Housing instability also contributes to substance use and victimization, circumstances that are linked to mental illness [16, 17]. Conversely, research has shown that housing improves mental health, making it a critical component to providing mental health treatment that has the potential to support long-term housing stability [15, 16]. The period of moving from homelessness to housing has been identified as a “critical time” for providing supports to improve mental health [18]. This may be particularly true in young adulthood, a period where many experience the onset of mental health symptoms [19], symptoms that can be exacerbated by housing instability.

## Service connection and treatment engagement

Young adults are less likely to utilize mental health services than both adolescents and older adults [3] and there is a precipitous drop in service use as youth take charge of their own care at age 18 [20]. YAEH are particularly impacted, with only one third getting mental health services in the previous year [21] despite demonstrated high need [2]. Barriers to service utilization are both perceptual and logistical. Among YAEH who screened positive for a mental health problem, 65% did not perceive that they had any mental health concerns, highlighting the need for developmental interventions that increase awareness and decrease stigma [22]. In addition, YAEH face barriers to successfully engaging in services even when they do identify the need, including uncertainty about where to go, transportation barriers, cost of care, lack of child care, and lack of flexibility in the hours and processes of providers [23]. The point of transition from transience to housing stability presents an opportunity to identify mental health needs and establish new connections to mental health services that can be supported and sustained over time.

Even when young adults receive services, however, they have high rates of treatment dropout. In one study following psychiatric hospital discharge, 50% of young adults did not follow up with treatment, and being African American was associated with increased risk of non-follow-up [24]. Barriers to treatment engagement specific to young adults have been identified and can be targeted to increase engagement [25]. These include negative beliefs or stigma of mental illness, fear, hopelessness, ambivalence, and self-image considerations [26, 27]. Prior research has developed and tested interventions to target these mechanisms, with emerging evidence of success [26, 27]. Specifically, young adults that participated in a group-based engagement intervention demonstrated greater treatment engagement (Cohen’s *d* = 0.59), decreased stigma (Cohen’s *d* = 0.47), increased trust in providers (Cohen’s* d* = 0.51), and more positive beliefs about mental health services (Cohen’s *d* = 0.57) compared to youth that received treatment as usual [28]. Connections to mental health services need to be paired with engagement interventions for young adults to achieve the benefits of treatment.

## Housing first approaches

Housing first approaches can be beneficial for stabilizing mental health and housing. The housing first model has emerged as the standard intervention approach for providing housing to adults with serious mental illness [30, 31]. This unconditional approach to housing has been less well studied in young adults but a randomized controlled trial for adults in Canada found that younger adults had different housing needs than older adults [32]. Compared to older adults in the trial, young adults entered with higher rates of substance use disorders, exposure to victimization, greater unmet needs for health care, and lower educational attainment [32]. These studies highlight the need to think about young adults as a specific population in need of tailored housing supports.

Rapid Rehousing (RRH) is a housing support model that provides housing subsidies paired with case management with the aim of stabilizing housing and providing service connections in a time limited fashion [33]. Across programs, this model provides housing navigation, subsidized rent for a discrete period, and case management [33]. But, there is little consistency across programs in the supportive services provided. Communities across the country have developed a range of approaches to supporting young adults in these programs but few have focused specifically on mental health treatment and engagement in the context of RRH [34–37]. Most recently, in 2017, HUD introduced a new housing model specifically for young adults that pairs more supported, structured housing delivered in a transitional housing program with rapid rehousing, giving young adults more flexibility to gradually transition to the less structured format of RRH [38]. The current study seeks to test an adapted version of the evidence-based Critical Time Intervention [39] for YAEH making a transition from homelessness to supportive housing in a time-limited housing program model such as TH/RRH. We integrated components of an evidence supported intervention for young adults with mental health challenges, Cornerstone Coordinated Community Care (C4) [29] to develop the adapted intervention called *Charge Up!*.

## Building on interventions with evidence in other populations

Critical Time Intervention (CTI) is a phased care coordination intervention that aims to connect individuals to formal and informal supports at a point of transition [39]. CTI identifies targeted time-limited intervention applied at critical transition points as a mechanism for enhancing the efficacy of long-term supports for persons with SMI who are living in the community [18]. CTI has been found to improve a range of outcomes for racially diverse adults with severe mental illness, including preventing homelessness, rehospitalization, and substance misuse after psychiatric hospital discharge [40–42]. CTI is delivered in three phases with decreasing intensity of contact at each phase. The first phase provides the most intensive support as the individual makes the transition that is the focus of the intervention. The focus in this phase is connecting the individual with a broad range of formal and informal support, including long-term supports that can remain in place after the intervention. In the second phase, the CTI case manager continues to provide support but encourages the person to solve problems with the assistance of their support network. In the third phase, the CTI case manager is intentionally stepping back and transferring responsibility to the individual and the long-term supports in their network [39].

Cornerstone Coordinated Community Care (C4) is specifically designed to increase engagement in mental health care and decrease mental health symptoms among adolescents and young adults [29, 43]. It is a psychosocial intervention that combines trauma-focused cognitive behavioral therapy, skills groups, Critical Time Intervention (CTI), and peer support providers called Recovery Role Models to serve youth with mental health challenges [29]. C4 primarily is designed to address engagement in treatment through impacting key targets (i.e., stigma, hope) and mental health symptoms and functional outcomes. The dual provider team of a licensed clinician and a peer provider works both in the clinic and in the community providing case management (i.e., CTI), in vivo supports, therapy and medication management, and skills groups. C4 was evaluated in a small-scale, two-group RCT using a pre-test/post-test design focused on engagement, symptoms, and functional outcomes. The study showed promising results related to decreases in symptoms, improved recovery, along with high feasibility and acceptability in a racially diverse sample of young adults in New York City [44].

## Guiding theoretical framework

Prior research has identified that interventions for YAEH need to provide an array of supportive services to accompany housing models [45], yet it is currently unclear the types and models of supportive services that may be most beneficial. We began with CTI as a starting point for intervention adaptation. In prior RCTs, CTI has been found to be effective for stabilizing housing in adults with serious mental illness, with some evidence that the hypothesized mediators of connections to family [46] and increased continuity of care [41] are critical targets for success. For young adults with mental health problems who are often not currently in treatment, connection to mental health services paired with support to ensure engagement in treatment are critical. Building on evidence from Cornerstone, *Charge Up!* integrates activities to enhance treatment engagement and connections to services including individual sessions in the community with a peer mentor and addressing socio-emotional needs with a mental health professional. Figure 1 provides the target framework which informs the *Charge Up!* intervention and the measurement of primary outcomes of mental health symptoms and housing stability, the secondary outcome of treatment engagement, and the assessment of whether the intervention is effectively addressing the hypothesized mechanisms of change – reduced stigma, increased hope, connections to services (including mental health services), community connections, family and other natural supports, and self-efficacy.

**Fig. 1 Fig1:**
[figure not shown]
Target framework for adapted charge up intervention

## The current study

This study aims to rigorously refine and conduct feasibility testing of a newly adapted version of CTI for young adults moving into supported housing that was developed by our team, entitled *Charge Up!* (originally called CTI-YAMH). *Charge Up!* adapts CTI for the specific context of transitioning from homelessness to TH/RRH for young adults and integrates the team approach and the mental health specific content from Cornerstone Coordinated Community Care (C4). The study embeds experimental therapeutics [47], focusing on exploring change mechanisms which have been targeted by CTI and C4 and that have been associated with improved treatment engagement, mental health, and housing stability in prior work. Experimental therapeutics which have been referred to as the science of “how” places focus not just on the impact of the intervention on the primary outcomes but also specifying the specific mechanisms that are hypothesized to result in the change and to rigorously examine and test which of these mechanisms is changing as a result of the intervention and whether that change is ultimately related to change in the primary outcomes.

The aim of this study is to conduct a phased open feasibility trial of the adapted *Charge Up!* Intervention, first refining the intervention (*n* = 8), and then testing it in a small randomized trial (*n* = 52) to assess acceptability, assess the feasibility of the intervention and randomization procedures, refine outcome measures, and conduct exploratory analyses to examine the preliminary signal of impact of the intervention. Through this work, we aim to assess the feasibility and acceptability of the intervention and explore whether it shows promise for improving our proposed mediating targets as well as our proposed primary and secondary outcomes—treatment engagement, housing stability and mental health symptoms. We also aim to better understand the feasibility challenges of conducting a randomized trial within the context of an existing housing interventions.

## Methods

### Study Design

The study employs a phased, open trial to first refine the intervention and procedures, then further test feasibility in a small randomized controlled trial of the refined intervention (see Table 1). The design of this feasibility pilot will enable us to examine several issues that we anticipate will need refinement prior to larger scale testing. First, we aim to understand the feasibility and acceptability of the intervention within the context of an existing housing intervention program. Through our first phase, we will focus on assessing the feasibility and acceptability of the proposed intervention, focusing specifically on refining procedures for team coordination and communication, documentation protocols, and developing fidelity measures. We will also examine commonly identified assessment targets for feasibility studies [48], including acceptability, demand for the intervention, practicality of the intervention, and feasibility of integration into the current housing system.

**Table 1 Tab1:** Randomized feasibility trial of Enhanced Housing Support Intervention, Charge Up! (*n* = 52)

	STUDY PERIOD							
	Enrollment	Allocation	Post-allocation				Close-out	
TIMEPOINT**	*-t*_*1*_	0	*t*_*1*_ _baseline_	*t*_*2*_ _3 month_	*t*_*3*_ _6 month_	*t*_*4*_ _12 month_		*t*_*x*_
Enrollment:								
Eligibility screen	X							
Informed consent	X							
Allocation		X						
Interventions:								
*Charge Up!*								
*Housing support as usual*								
Assessments:								
Mental health diagnoses	X					X		X
Mediating targets			X	X	X	X		X
Mental health symptoms and housing stability			X	X	X	X		X
Fidelity assessment				X	X			X

We will also assess aspects of the research methods and measures in preparation for conducting a larger randomized trial. The first key issue is randomization. Because the *Charge Up!* intervention is implemented for young adults with mental health issues who are transitioning from homelessness to supported housing in the TH/RRH program, randomization needs to occur at the point of assignment to an agency for TH/RRH. The primary agency who partnered with us to develop the intervention, is one of several agencies in the area that provides TH/RRH services for young adults. Because randomization is happening in the context of assignment to services, we need to determine the optimal time to screen and enroll participants in the study so that there is the ability to randomize when a spot becomes available. Second, we will assess and document the suitability of the control condition, treatment as usual (TAU), which is conducted system wide at agencies that provide young adult TH/RRH. There is variation in how TH/RRH is implemented across agencies in the community in the length and setting (scattered vs congregate) for the program.. A third key issue of the feasibility pilot is the refinement of measures. Measures of our mediators were selected based on CTI research in adult populations and may need refinement for young adults, so we will examine multiple measures for several constructs, examining internal consistency with Cronbach’s alpha. We will also explore additional ways to measure several mediators beyond self-report through documentation procedures of team members and administrative data that can provide additional measures of the constructs. We will also conduct exploratory analyses using correlations to see whether our measures are related to each other as we hypothesize they will be. Finally, we will conduct process mapping and team-based costing activities to estimate the costs of the intervention. Together, examination of these specific areas will provide important information that will prepare us to conduct rigorous testing of the intervention in a future larger randomized trial.

### Sample

Our sample will include young adults (age 18–24) who have qualified for TH/RRH supports, an eligibility determination that happens based on their score on a vulnerability index administered when they are placed on the housing waitlist. Young adults are assigned to a case manager based on capacity across agencies that provide TH/RRH. For phase 1 of the feasibility trial (*n* = 8), we will work with our partner agency to enroll young adults as they transition into the TH/RRH program. Referrals for this first phase will be provided by our partner agency and we will work closely with the case managers at this agency to refine our procedures and refine the intervention as we learn during this first phase. We will also use this first phase to refine the measures for the study. Structured interviews will be administered by a trained member of the research team at baseline, 3 months, 6 months, and 12 months.

For the second phase of the study, we plan to expand the intervention to be available at any of the three agencies in the community that offer TH/RRH. We will identify young adults who qualify for the *Charge Up!* intervention in conjunction with their prioritization for housing. The screening tool used to prioritize assignment to housing asks for a self-report of lifetime mental health diagnoses, and we will add the Kessler-6 to screen for current mental health problems. Those that report prior mental health diagnosis or screen positive for current symptoms will be eligible for *Charge Up!* and will be provided with information about the study. Those that are interested will meet with a member of the research team for an intake and participate in a baseline interview. The intake packet will contain a card which has information about randomization prepared using a random numbers table, which will be opened following the initial assessment. We will closely track the feasibility of this process, keeping track of the number of YAEH who are on the wait list, the number contacted, the number successfully enrolled, and the number that meet our enrollment criteria.

For the first phase of the open trial, we aim to recruit a sample of 8 young adults who are receiving TH/RRH services at our partner agency. During the second phase of the trial, we will expand recruitment to enroll 52 young adults with mental health history or symptoms and randomize half to each condition. Based on current housing capacity and our prior research, we estimate that 60–75% will screen positive for mental health problems as assessed with the Kessler-6 or prior history so at current capacity we would identify 4–6 participants per month that are eligible for the study and enroll 2–3 of these for approximately 12 months in the intervention condition and 2–3 participants per month for 12 months in the TAU condition.

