### Eligibility determination and retention

Young adults (age 18–24) will be screened for study inclusion criteria (meeting criteria for psychological distress on Kessler-6 [49] or self-reported prior diagnosis of depression, anxiety, bipolar or a psychotic disorder) and invited to participate at the point of assignment to a TH/RRH program. Young adults will be told of the opportunity to participate in the study at the time of intake to a program and asked for permission to provide their names to the study team if interested. When the young adult meets the centralized housing criteria that qualifies them for TH/RRH, they are referred to a receiving agency who will provide names to the study team. The team will screen for eligibility and schedule a baseline interview. Trained graduate-level research assistants from the study team will obtain informed consent and administer the survey in person or via phone or Zoom. In order to track outcomes through the course of the 6-month intervention, we will administer surveys at baseline, the midpoint (3 months), end of the intervention (6 months) and follow-up 6 months later (12 months). We will also conduct qualitative interviews with all young adults in the first phase of the feasibility pilot (*n* = 8) and each of the professionals involved in implementing it (*n* = 5) to explore qualitatively assess implementation outcomes of acceptability and appropriateness. Interviewers will contact all young adults in both conditions of the trial monthly to maintain contact and increase retention. At the time of enrollment, a locator form will be completed to gather detailed data about contact information including social media contacts and the names of others who may know how to contact the young adult. Participants’ incentives for completing study interviews increase over time with the aim of increasing retention.

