### Data management and analysis

Qualitative data will be digitally recorded, then transcribed and stored on a secure data platform. Quantitative data will be collected using Qualtrics and stored on the secure data platform. Participant data will have a study participant number but no other identifying information and will be stored on the secure platform in a password protected file separate from identifying information. Structured interview data will be reviewed regularly by the study team for completeness and examined for missing values or outliers.

For the qualitative analysis focused on feasibility and acceptability of the *Charge Up*! intervention, we will analyze open-ended responses from participants at each survey administration and transcripts of interviews with participants and intervention staff using thematic content analyses [75]. A team of coders will develop a codebook through iterative discussions, then code interviews and examine common themes across the sample [76]. Preliminary results will be shared with participants (YAEH and staff) in a member checking process and compared with the quantitative results on the implementation outcomes measures. Intervention procedures and study measures will be modified based on feedback received in the first phase of the feasibility study for further testing and exploration in the randomized feasibility pilot in phase 2.

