## Summary and future directions

There are a few limitations that should be considered in relation to this pilot trial. The fact that the *Charge Up!* intervention is delivered in conjunction with existing housing programs introduces variation that may impact our target outcomes of housing stability and improved mental health. While all programs in the community are providing TH/RRH, they vary in the type of housing provided (on-site vs. scattered site) and their flexibility in the length of time they aim to provide housing support. We will collect data and document the impact of the housing program and its rules and supports on outcomes as we conduct the trial. Ideally, randomization will allow us to see whether *Charge Up!* has an effect on our outcomes when comparing young adults who received housing within the same housing program as well as comparing all young adults by condition across housing programs. It is also not possible to blind young adults or interviewers to the intervention condition, which is a potential limitation that could influence reporting of outcomes by young adults and assessment of outcomes by interviewers. We will provide training to interviewers and raise this issue within the training to help mitigate this potential bias.

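### The assignment card sits in the intake packet, so concealment rests on the enrolling team's own timing rule, and Table 1 contradicts that rule's order

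*Protocol article*

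**What the plan says.** All references are to the protocol article.

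- **Where the assignment is kept and when it is revealed** (Methods, Sample): "The intake packet will contain a card which has information about randomization prepared using a random numbers table, which will be opened following the initial" (that is, once the first assessment is done).
- **Who runs the intake** (same section): "Those that are interested will meet with a member of the research team for an intake and participate in a baseline interview".
- **Who screens** (Eligibility determination and retention): "The team will screen for eligibility and schedule a baseline interview".
- **Who consents and interviews, and how** (same section): "Trained graduate-level research assistants from the study team will obtain informed consent and administer the survey in person or via phone or Zoom".
- **Allocation target** (Sample): "enroll 52 young adults with mental health history or symptoms and randomize half to each condition".
- **Order of events in the schedule** (Study Design, Table 1): the column groups run "Enrollment Allocation Post-allocation". Allocation is at time 0, and the baseline time point t1, with the symptom, housing and mediator measures, is the first column under the last of these headings.

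Study Design names randomization as the first key methodological issue. Sample size and quantitative analysis makes the feasibility of recruitment and randomization procedures a primary objective and calls the remaining analyses exploratory. Table 4 bases its recruitment criterion on the share of those approached who accept randomization and enrol.

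**The concern.** Each assignment is drawn in advance and placed in the material used at the intake meeting. It is therefore with the research team before the baseline interview is finished and, if consent is taken at the same meeting, before consent. The only barrier the article states is a rule about when to open the card, and the team that enrols is the team that applies it. In a remote baseline the participant is not in the room and cannot readily confirm the moment of opening or which card was used.

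Two things are at stake. First, the randomization procedure is one of the things being piloted; if concealment depends on staff discipline, the pilot may report the method as workable without having tested whether it conceals. Second, if an assignment were known early, a deferral or a lapse before consent could depend on the arm. That would alter the Table 4 recruitment percentage and the comparability of the arms behind the preliminary signal of impact.

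**Working it through.** **1. No stated figure depends on this point.** The one interval tied to N = 52 in the randomized phase's retention objective reproduces: 0.70 ± 1.96 × √(0.70 × 0.30 / 52) = 0.70 ± 0.125, or 57.5% to 82.5%, against 57.6% to 82.4% stated. It is unaffected. The rest is mainly a comparison of passages.

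**2. What is exposed and what is not.** In Sample, a prior diagnosis or the Kessler-6 settles eligibility and the young adult expresses interest before the intake meeting. Eligibility determination and retention likewise has screening first and the baseline interview scheduled afterwards. So eligibility and first interest precede the packet. What can overlap with it is consent and the baseline interview.

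**3. The order of opening.** Sample: intake, baseline interview, card opened after the initial assessment. Table 1: allocation at 0, then baseline at t1. If the initial assessment is the baseline interview, the two orders conflict. If it means only the diagnostic assessment that Table 1 places in the enrolment column, the baseline symptom and housing reports would be taken with the arm already known. The article does not say which is meant.

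**4. Predictability of the next assignment** (assuming a forced 26:26 list where one applies):
- card readable in advance: 100%;
- card concealed, simple randomization: 50%;
- card concealed, 26:26 forced, all past assignments known: 30.04 expected correct guesses out of 52 = 57.8%.

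Access to the card is what matters most; the list structure adds little.

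**5. Table 4 boundary** (taking those approached as the denominator in every column). With 52 enrolled, 52/69 = 75.4% is PROCEED and 52/70 = 74.3% is AMEND. Near the boundary, one person approached but not enrolled for an arm-dependent reason changes the category.

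**6. Illustration of bias; the steering fraction and correlation are assumptions.** Suppose that in a fraction f of enrolments the more distressed half goes to *Charge Up!*. The mean of the upper half of a standard normal is 0.798, so the expected baseline gap is 2 × 0.798 × f SD:

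| f | Gap (SD) |
|---|---|
| 10% | 0.16 |
| 20% | 0.32 |
| 30% | 0.48 |

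With an assumed baseline-to-follow-up correlation of 0.5 to 0.7, f = 20% carries 0.5 × 0.32 = 0.16 to 0.7 × 0.32 = 0.22 SD into follow-up with no true effect. In this direction *Charge Up!* would look worse on symptoms; steering the other way would flatter it. I give no false-positive rate, because the article describes no between-arm significance test.

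**The case against.** The case on the other side is substantial, and much of it stands.

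- A card that is opened was closed before. Assess first, reveal second is the right order, and following it protects the assignment. Sealing, opacity, numbering and logging are details an article commonly leaves to the full protocol, so their absence here is no finding.
- A reader might infer that unblinded staff know the coming assignment. The documents do not support that. The statement that "It is also not possible to blind young adults or interviewers to the intervention condition" (Summary and future directions) concerns influence on the reporting and assessment of outcomes, not knowledge of an unopened card.
- A reader might also infer that eligibility decisions are exposed, or that one person carries the packet through every step. Screening comes before the packet, and the text speaks of the team and of a member of it, so a single handler is an inference.
- Room to delay or reorder is limited: entry follows a centralized, prioritized wait list, and 4–6 eligible participants are expected per month.
- The steering fraction has no source in the documents, and effect estimation is not the pilot's objective.
- The article promises to track the feasibility of the process.

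Two things survive. The listed tracking counts (wait list, contacted, enrolled, meeting criteria) would not show when or by whom a card was opened. And the article does fix where the card is kept: even with sealed, numbered cards, the assignment would stay with the enrolling team with no independent release, and the Table 1 conflict would remain.

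**Conclusion.** The point holds as a weakness in a stated mechanism, together with an internal contradiction about order. Concealment relies on enrolling staff keeping to a timing rule, remote baselines make that rule hard to verify, and Table 1 places baseline after the allocation that Sample places after the assessment. The documents do not show that anyone will know an assignment early or that results will be biased; a reader who concludes that goes further than the text. The 0.16 to 0.48 SD baseline gaps rest wholly on an assumed f of 10% to 30% and only show scale. The consequence for the exploratory effect analyses is moderate. The main reason to act is that the randomization procedure is a primary feasibility object and feeds the recruitment criterion. This is worth changing as a cheap improvement; it does not invalidate the design.

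**What to change.** In Sample, remove the card from the intake packet. Release each assignment from a list that enrolling staff cannot see, only after consent is recorded and the baseline form is submitted, with a time stamp and the participant number. The list can be loaded in the electronic system (the article says "Quantitative data will be collected using Qualtrics and stored on the secure data platform"; whether that platform can hold a concealed list needs checking) or kept by an existing team member who neither enrols nor interviews. Count a participant as randomized from the moment of release. The same procedure serves in-person, phone and Zoom baselines. Reconcile Table 1 with Sample so that baseline and allocation appear in one order, and say what the initial assessment comprises.

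Cost: a minor IRB amendment, reported to the DSMB as Ethics and dissemination requires; some system set-up or a small duty for the list holder; and a connection or call before the participant is told the result. No extra participants or visits are needed.
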